## Abstract

**Background:**

Multimorbidity, polypharmacy, and older age predispose seniors to adverse drug events (ADE). Seniors with an ADE experience greater morbidity, mortality, and health care utilization compared to their younger counterparts. To mitigate and manage ADEs among this vulnerable population, we designed a geriatric pharmacology consultation service connecting clinicians with specialist physicians and pharmacists and will investigate the feasibility and acceptability of this complex intervention in the long-term care setting, prior to conducting a larger efficacy trial.

**Methods/Design:**

We will conduct a cluster randomized feasibility trial and qualitative analysis of GeriMedRisk among four long-term care homes in the Waterloo-Wellington region from May 1 to December 31, 2017. The primary outcome is the feasibility and acceptability of GeriMedRisk and the stepped-wedge cluster randomized controlled trial design. We hypothesize that GeriMedRisk is a feasible intervention and its potential to decrease falls and drug-related hospital visits can be evaluated with a stepped-wedge cluster randomized controlled trial design.

**Discussion:**

This mixed methods study will inform a larger efficacy trial of GeriMedRisk’s ability to decrease adverse drug events among seniors in the long-term care setting.

**Ethics and dissemination:**

The Hamilton Integrated Research Ethics Board granted the approval for this study protocol 2812. We plan to disseminate the results of this study in peer-reviewed journals and also to our partners and stakeholders.

**Trial registration:**

ISRCTN clinical trials registry, ISRCTN17219647 (March 27, 2017)

## Background

Every year, tens of thousands of seniors experience a poisoning or adverse drug event (ADE) [1, 2]. Multiple diseases, polypharmacy, and age predispose older adults to drug toxicity. Following a poisoning, seniors (aged ≥ 65 years) are four times more likely to die or to require hospitalization compared to their younger counterparts [3]. Drug toxicity is costly, with at least $13 million spent on ADE-related hospital visits among seniors and $419 million spent annually on potentially inappropriate medications in North America [1, 4]. Decreasing polypharmacy may prevent ADEs among seniors. Studies of deprescribing interventions among older adults found improved quality of life and decreased hospitalization and mortality [5]. Widespread application is limited, however, by inadequate systems of care integrating primary care, pharmacy, geriatric medicine, and clinical pharmacology [6, 7]. Pharmacist-led medication review services to assess medication appropriateness include the Medscheck and the Pharmaceutical Opinion Programs. The Ontario Pharmacy Research Network (OPEN), however, found that a minority of patients receiving a Medscheck were older and medically complex and that there was a discrepancy in the quality of the delivered service, and there was no evidence of improved patient outcomes [8]. Furthermore, existing deprescribing algorithms and apps may not apply to patients with multimorbidity or mental illness, a group vulnerable to ADEs [9]. The majority of expertise in geriatric pharmacology is concentrated in urban academic health sciences centers resulting in inequitable access for Canadians residing in rural and remote areas [10]. There is a need for a timely and cost-effective geriatric pharmacology consultation service for Ontario seniors irrespective of their location.

Telemedicine, or telehealth, is the use of communication technologies to deliver patient care and medical services remotely [11]. It enables the delivery of health care services to areas that are remote or that have insufficient clinicians and resources [11]. Telemedicine tools include telephone and computer- or mobile device-based videoconference or eConsult [11, 12]. Its use improves access to care, support from specialists to primary care, and potentially decreases health care costs [11, 13–15]. Telemedicine services have been able to increase access to specialist clinician services for toxicology through poison centers, stroke, psychiatry, dermatology, and hepatic disease [11, 16–19]. With the limited number of clinicians with specialization in geriatrics, telemedicine may be a potential solution to serve the increasing aging population [10, 14, 15].

GeriMedRisk is a novel interdisciplinary, technology-based geriatric pharmacology consultation service that aims to optimize a patient’s medications to improve cognition, mobility, function, and mental health by supporting their clinicians. Referring clinicians will be able to easily access GeriMedRisk nurses, pharmacists, and physicians specializing in geriatric medicine, clinical pharmacology, and geriatric psychiatry by telephone or through telemedicine. By supporting clinicians as they optimize their complex older patients’ medications, GeriMedRisk has the potential to decrease drug-related cognitive impairment, falls, and hospital visits among seniors from all clinical settings. Prior to conducting an efficacy trial of GeriMedRisk to decrease adverse drug events across 14 long-term care (LTC) homes in Southwestern Ontario, we will first test the feasibility of the service and proposed study design, a stepped-wedge cluster randomized controlled trial.

The aim of this study is to investigate the feasibility and acceptability of the GeriMedRisk and its evaluation with a stepped-wedge randomized controlled trial in the long-term care (LTC) setting. We also intend to identify indicators of a difference in falls and drug-related hospital visits among seniors residing in LTC with access to GeriMedRisk compared to those without. We hypothesize that GeriMedRisk is a feasible intervention, and its potential to decrease falls and drug-related hospital visits can be evaluated with a stepped-wedge cluster randomized controlled trial design.

## Methods

This protocol (version 4.0, March 27, 2017) was developed in concordance with the Standardized Protocol Item: Recommendations for Interventional Trials (SPIRIT) checklist and CONSORT extension [20] to pilot trials and is registered with the ISRCTN clinical trials registry (ISRCTN17219647). The trial sponsor is McMaster University located at [name].

### Setting

We will conduct this study across a convenience sample of four LTC facilities in the Waterloo-Wellington region, Ontario, Canada, with each site serving as a cluster. The Waterloo-Wellington region has a population exceeding 775,000 residents and encompasses the major urban centers of Waterloo, Kitchener, Cambridge, and Guelph. While 90% of the geography is rural, 90% of the population lives in urban areas. The population of Waterloo-Wellington has similar demographics as the rest of the province of Ontario [21]. At each site, residents are assigned to a primary care doctor or nurse practitioner. Each site is supported by a consultant pharmacist who performs medication reviews at full-time equivalents ranging between 0.25 and 0.3. The three Schlegel Village LTC homes have uniform physical environments and philosophies of care but individualized staffing and clinical programs. University Gates Schlegel Village is a 192-bed LTC home located in Waterloo, supported by primary care clinicians and regular on-site geriatric medicine and geriatric psychiatry consultants. Winston Park Schlegel Village located in Kitchener is a 95-bed facility supported by a primary care clinician and an on-site geriatrician consultant. Riverside Glen Schlegel Village is a 192-bed LTC home located in Guelph that does not have designated support from a geriatrician. LTC patients that require a geriatrician are referred through a centralized intake process through the Waterloo Wellington Specialized Geriatrics Services. St. Joseph’s Health Centre Guelph, a non-profit 244-bed facility, is supported by primary care physician and an on-site consultant geriatrician.

### Eligibility criteria

Inclusion criteria:Cluster: a convenience sample of LTC homes in Waterloo-Wellington region that expressed interest in participating in this feasibility study.Individual participants: all physicians, pharmacists, and nurse practitioners who provide patient care in a participating LTC site when they are allocated to the intervention.

Exclusion criteria:There are no exclusion criteria for LTC clinicians or residents.

Criteria for discontinuing the intervention:If the referring clinician’s patient status is an acute poisoning (defined as an ingestion of more than two times the prescribed dose), or clinically unstable, GeriMedRisk will abort the call and encourage the clinician to call either the Ontario Poison Centre and/or emergency services.

### Intervention

In addition to the usual Waterloo-Wellington regional geriatric services, clinicians caring for seniors with medication challenges will have access to GeriMedRisk. GeriMedRisk is an interdisciplinary, technology-based geriatric pharmacology consultation and review service. It aims to optimize a patient’s medications to improve cognition, mobility, function, and mental health by supporting their clinicians. Referring clinicians will be able to easily access GeriMedRisk nurses, pharmacists, and physicians specializing in geriatric medicine, clinical pharmacology, and geriatric psychiatry by telephone or through telemedicine during business hours. Input from the following informed GeriMedRisk’s development: long-term care residents and their caregivers; Waterloo-Wellington region health administrators; the Ontario Poison Centre, a provincial service that uses telemedicine to deliver toxicological expertise to the public and clinicians in Ontario, Canada; the Ontario Telemedicine Network; and Champlain BASE eConsult and a needs assessment of Waterloo-Wellington physicians, nurse practitioners, pharmacists about geriatric pharmacotherapy.

Participants have two options for methods for referral:Telephone: this traditional mode of person-to-person consultation can be either real-time or delayed by a few hours if used as a paging service whereby the referring clinician leaves a call-back number.eConsult: the referring clinician sends an eConsult with the patient’s necessary clinical information through a private and secure portal through the Ontario Telemedicine Network (OTN) at www.otnhub.ca to GeriMedRisk [12]. The GeriMedRisk team responds within five business days through eConsult with a request for additional information or recommendations. Additional support through the phone, OTN videoconference or in-person may be arranged if necessary.

The GeriMedRisk staff will collaborate with the referring clinician to perform a geriatric pharmacology consultation and medication review or answer a geriatric drug information question. The former process utilizes components from a comprehensive geriatric assessment to address the patient’s cognition, comorbidities, mobility, function, and mental health and incorporates an intrinsic medication appropriateness assessment [22, 23]. Videoconference telemedicine and in-person consultations with specialist physicians across Southwestern Ontario academic health centers (McMaster University, University of Toronto, University of Western Ontario) would be available if necessary. Password-protected consultation reports and user-friendly drug information and knowledge translation materials will be securely sent to the referring clinician through OTN eConsult. These educational materials are concise evidence-based documents relevant to the consult that serve to build geriatric pharmacotherapy capacity among referring clinicians. Their development is in accordance with rapid review methodology described by the National Collaborating Centre for Methods and Tools [24]. GeriMedRisk will perform at least one follow-up to the referring clinician within 2 weeks to assess the effectiveness of the recommendations and monitor adherence. During the duration of the study period, all LTC sites would continue to have access to their usual local and regional geriatric services. There will be no restrictions in concomitant care and interventions. The control period is defined as the 12-month period preceding the day the LTC’s clinicians acquired access GeriMedRisk.

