### Study design

We will conduct a mixed methods feasibility study using an exploratory framework. The quantitative component will be a stepped-wedge cluster randomized controlled trial. All study sites will have uniform access to their usual Waterloo Wellington Local Health Integration Network geriatric services. Using a computer-generated sequence and simple randomization techniques, we will randomize the order of when each site acquires access to GeriMedRisk. Every 8 weeks, a new site will gain access to the intervention until all four LTC sites have access to the intervention (Fig. 1). This time period allows for the orientation and potential adoption of GeriMedRisk and telemedicine technology prior to introducing the next site.

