**Fig. 1 Fig1:**
[figure not shown]
Schematic of study protocol. Each step from T0 to T3 will be approximately 8 weeks in length. Each cell starting at T0 represents a data collection point. Prior to T0, secondary outcomes will be collected retrospectively collected using the RAI-MDS 2.0. Yellow-shaded cells represent the recruitment period. During this time, LTCs will be invited to participate and will be provided trial information. Consent will be obtained from each LTC. Subsequently, investigator will provide in-person and online information sessions about the trial to potential participants (i.e., clinicians of the participating LTC site), and consent will also be obtained. Randomization (red line) will occur at the beginning of the first step, T0. The GeriMedRisk intervention (dark blue cells) will then be introduced to each LTC in random order. At the beginning of each step, a sealed envelope will be opened to reveal the next LTC to receive the intervention. An interim analysis (green line) will be performed at 16 weeks

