#### Secondary outcomes

The core outcome set for effectiveness trials aimed at optimizing prescribing in older adults in care homes informed the selection of our secondary outcomes [28, 29]. These outcomes are clinically relevant, potentially modifiable, well-validated in the MDS-RAI 2.0, and in some cases, a surrogate marker of care [30–32]. For these same reasons, Health Quality Ontario, a provincial body that advises on the quality of health care provided, also uses these outcomes as long-term care quality indicators [32]. We will assess the completion of our secondary outcome data regarding each LTC site’s monthly rates of falls, hospital visits, and medication appropriateness. Using the Resident Assessment Index Minimum Data Set (RAI-MDS) 2.0, we will examine the following in the 1-year lookback period prior to the date of the intervention’s introduction and monthly thereafter [30]. We will examine each LTC site’s monthly incidence of falls and injurious falls and emergency hospital visits. We will include all-cause mortality and those associated with adverse drug events or falls [28]. We will characterize the proportion of LTC residents receiving potentially inappropriate medications defined by the Beers Criteria and STOPP/START criteria [4, 33], psychotropics (defined as a sedative-hypnotic, antidepressant, antianxiolytic, antipsychotic, lithium or antiseizure medication in the absence of a seizure diagnosis), and long-acting opioids.

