### Data collection

#### Primary and secondary outcomes

The primary outcomes of this study include the acceptability and feasibility of GeriMedRisk and the stepped-wedge cluster randomized controlled trial. These include factors influencing the successful implementation of the GeriMedRisk service in terms of feasibility and acceptability among users and non-users and staff providing the GeriMedRisk service. Secondary outcomes include the LTC site’s monthly rate of falls, hospital visits, and medication appropriateness. We will measure secondary outcomes in the 52-week period preceding the commencement of GeriMedRisk access (defined as day − 365 to the first day of access to GeriMedRisk) and after, on a monthly basis for each site. These pre-specified outcomes will be systematically collected from our project-specific database from the OTN eConsult database, telephone records, RAI-MDS 2.0, and physician billings.

The Ontario Telemedicine Network (OTN) database is an administrative database that contains physician contact information and specialty and dates of engagement with GeriMedRisk. We will utilize telephone records as measured by the Voice Over Internet Protocol telecommunications manager, Vertical Summit®, to capture call volumes, dropped calls, and ring, queue, and call times. We will use the RAI-MDS 2.0 data for each LTC site. This standardized assessment tool is routinely applied to all LTC residents in Ontario, Canada, upon LTC admission, readmission from the hospital, change in status, and on a quarterly basis [30–32, 34]. It captures demographical and clinical information that is frequently used in observational research and quality improvement initiatives. We will use de-identified and anonymized aggregate data from the RAI MDS for each LTC site. We will also use aggregated, anonymized, and de-identified LTC pharmacy records to obtain information about prescription and non-prescription medication use.

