### Statistical data analysis

#### Quantitative analysis

As the main objective of this study is to evaluate the feasibility of GeriMedRisk and its stepped-wedge cluster randomized trial design, we will describe the primary outcomes in a narrative analysis with 95% confidence intervals (CI) where appropriate. We define success or acceptability of GeriMedRisk as a composite of either 60% adherence to GeriMedRisk recommendations or at least 20% of each LTC sites’ physicians making more than one consult to GeriMedRisk during the study period (May 1, 2017, to December 31, 2017).

For the secondary outcomes, we will assess each LTC site’s outcomes, described as monthly rates, in the 12 months preceding the intervention (baseline) between clusters pre-intervention and calculate the intercluster variance. We will assess for intra- and intercluster differences in the secondary outcomes, described as each LTC site’s monthly rates, with weighted generalized linear mixed models. This definition will guide our interpretation of the study’s results and potential modifications to the GeriMedRisk intervention or subsequent larger efficacy trial’s protocol.

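### Taking each home's own preceding 12 months as control, with no calendar-time term stated, makes the secondary-outcome contrast a before-after one open to trend and season

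*Protocol article*

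**What the plan says.** The comparator is fixed in the Intervention section: "The control period is defined as the 12-month period preceding the day" on which that home's clinicians gained access. The same window recurs under Secondary outcomes ("in the 1-year lookback period prior to the date of the intervention’s introduction and monthly thereafter"), under Data collection ("We will measure secondary outcomes in the 52-week period preceding the commencement of GeriMedRisk access") and under Quantitative analysis, where the 12 months before the intervention are called baseline.

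Access dates are staggered in random order: "Every 8 weeks, a new site will gain access to the intervention until all four LTC sites have access to the intervention". The study period runs from 1 May to 31 December 2017.

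For analysis, differences within and between clusters are to be assessed on "monthly rates, with weighted generalized linear mixed models". No period, month or season term is mentioned, and no statement excludes one.

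**The concern.** Only the order of access is randomised. That protects the comparison when homes with and without access are compared in the same calendar time. A control made of a home's own previous year uses no concurrent home, so any drift in falls or hospital visits over the year, and any seasonal imbalance between the windows, is read as an effect of the service.

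Two stated uses are at stake. The study seeks indicators of a difference in falls and drug-related visits, and its results are to inform the sample size of the efficacy trial. The first could be biased, and the second would rest on a precision that a stepped-wedge analysis cannot reach.

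**Working it through.** The plan gives no figure of its own for this bias, so there is none to reproduce.

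**Inputs.** From the protocol: four homes with 192, 95, 192 and 244 beds (723 in all), 8-week steps, study period 1 May to 31 December 2017, a 365-day control window per home, an emergency visit rate of 25% and a target decrease of 20%. Assumed: the first home starts on 1 May 2017, data end on 31 December 2017, and the sizes of trend and season are as stated below.

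**Step 1: windows.**

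| Order | Access from | Control window | Control days from 1 May 2017 on | Post-access days |
|---|---|---|---|---|
| 1 | 1 May 2017 | 1 May 2016 to 30 Apr 2017 | 0 | 245 |
| 2 | 26 Jun 2017 | 26 Jun 2016 to 25 Jun 2017 | 56 | 189 |
| 3 | 21 Aug 2017 | 21 Aug 2016 to 20 Aug 2017 | 112 | 133 |
| 4 | 16 Oct 2017 | 16 Oct 2016 to 15 Oct 2017 | 168 | 77 |
| Total | | 4 x 365 = 1460 days | 336 | 644 |

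- Control site-days concurrent with an exposed home: 336/1460 = 23%. The other 1124 (77%) precede the trial.
- Intervention site-days with a concurrent unexposed home: (168 + 112 + 56 + 0)/644 = 336/644 = 52%. The last 4 x 77 = 308 have none.
- Post-access windows are 35, 27, 19 and 11 weeks. None contains a January-April day, and every control window contains all of them.

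**Step 2: secular trend.** The midpoints of a home's two windows lie (365 + post-access days)/2 apart: 305, 277, 249 and 221 days, or 0.836, 0.759, 0.682 and 0.605 years. With an assumed drift of -10% per year and no true effect, the homes show -8.4%, -7.6%, -6.8% and -6.1%. A model with site effects weights each home by (365 x post days)/(365 + post days), that is 146.6, 124.5, 97.5 and 63.6, and gives -7.5% pooled. With calendar-period effects added, the bias is 0.

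**Step 3: season.** Let rates be raised by a fraction u in four months. Bias = (1 + u x share of post-access days in those months) / (1 + u x share of control days in those months) - 1. Pooled over site-days:

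| Raised months | Post share | Control share | u = 10% | u = 20% | u = 30% |
|---|---|---|---|---|---|
| January-April | 0/644 | 120/365 | -3.2% | -6.2% | -9.0% |
| December-March | 124/644 | 121/365 | -1.3% | -2.6% | -3.8% |
| November-February | 244/644 | 120/365 | +0.5% | +0.9% | +1.4% |

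Single homes can differ more. For November-February and u = 30%, the last home has a post share of 61/77, so (1 + 0.3 x 61/77)/(1 + 0.3 x 120/365) - 1 = +12.7%. A smooth winter peak of 10% amplitude nearly cancels when pooled (-0.4%), but gives -2.9%, -1.9%, +1.4% and +5.7% by home in rollout order. Calendar-period effects bring the pooled bias to about 0.

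**Step 4: precision.** Assume Poisson counts, full beds, 0.25 visits per resident-year and a rate ratio of 0.8.

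- Without calendar time: control events 723 x 0.25 = 180.75. Post-access events, at the average of 644/4 = 161 days, are 723 x (161/365) x 0.25 x 0.8 = 63.8. SE of the log rate ratio = sqrt(1/180.75 + 1/63.8) = 0.146. Fitting site effects gives 0.148.
- With site and 28-day calendar effects on the protocol's own windows, averaged over the 24 possible orders: 0.294 to 0.295, about twice as large. Calendar months, with crossover months split, give 0.287.
- A separate calculation with independent errors gives a variance ratio of 4.1, hence the same factor (sqrt 4.1 = 2.0).
- Starting all four homes at 1 May 2016, with calendar effects: 0.284 to 0.285, about 3% smaller.

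**The case against.** The strongest reply is that the window definition does not by itself undo the design. Access is randomised and staggered, later homes' control windows run into the trial, and the mixed models are to cover differences between clusters as well as within them. A reader might infer that the stepped wedge has become a before-after study. The documents do not support that: the concurrent data in step 1 exist, and a calendar-time model on the protocol's own windows recovers the comparison.

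It can also be said that model terms belong in a statistical analysis plan, which is not shown. That is fair, and silence on a covariate would not be a finding alone. What stands is the definition of control, which the protocol states and repeats. An analysis plan with period effects would have to explain how it fits that definition.

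Three further inferences should not be drawn:

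- That season must favour the service. The -3% to -9% range needs a January-April peak; other winter patterns shrink the pooled bias or reverse its sign.
- That the Fig. 1 caption contradicts the definition. It says "Prior to T0, secondary outcomes will be collected retrospectively collected using the RAI-MDS 2.0", which describes how data are gathered and is compatible with windows that straddle T0.
- That the baseline between-cluster variance is distorted by season. Each 12-month window contains every calendar month once, so only drift over at most 24 weeks remains, and its effect on the variance has not been quantified.

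**Conclusion.** The point holds in limited form. The stated control, used with the stated model and nothing more, yields a contrast confounded with calendar time. The windows in step 1 follow from the protocol's dates and step length. The size of the bias does not: it rests on assumed trend and season, and its sign is uncertain for season. The loss of precision is firmer. Under the Poisson assumptions, allowing for calendar time doubles the standard error, so an analysis without it would give the efficacy trial intervals about half as wide as they should be.

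The 20% decrease is a useful yardstick for these biases, but it is a sample-size input and not a decision threshold. The primary outcome is feasibility and is described narratively, so the main conclusion of the trial does not depend on this contrast. The change is still worth making, because one aim is to learn whether the effect can be evaluated with a stepped-wedge design, and an analysis without calendar time does not test that.

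**What to change.** In the Intervention and Quantitative analysis sections, state that the effect on secondary outcomes is estimated from all site-months with and without access, placed on calendar time, with calendar-month fixed effects, a site effect and an access indicator. Split a month that contains a crossover, or code it by the fraction of the month with access. Calendar months suit the planned monthly aggregate data better than 4-week blocks, which might need a different extraction. Keep the comparison with each home's own 12 months as descriptive only.

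A common window from 1 May 2016 for all homes is optional. It needs 8 to 24 more weeks of retrospective data at three homes and changes the standard error by only about 3%; the model term does the work.

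The cost is a change of wording and, if crossover months are split, part-month counts at the homes concerned. The downside is wider intervals, which are the right ones to carry into the efficacy trial.
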